### 9.2 Sample Size Determination

Previous studies observed a reduction in systolic blood pressure of  $10.4 \pm 11.4$  mmHg after intake of olive extract [10,11]. A reduction in systolic blood pressure is the primary endpoint and is therefore used to determine the sample size.

Since another study will examine a different primary endpoint in participants from the placebo group of this study, an  $\alpha$ -level of 0.025 is used. The planned power is 80%.

It is calculated that at least 25 participants per group are needed to detect this effect. This calculation was performed using G\*Power 3.1. Considering an anticipated dropout rate of 10%, 28 participants per group (56 in total) will be recruited for this study.

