## 2. Introduction

### 2.1 Rationale

Cardiovascular diseases (CVD), such as stroke or heart attack, are among the leading causes of death worldwide, with 17.9 million deaths per year [1]. High blood pressure is the main risk factor for developing CVD. It is also an important risk factor for other conditions such as chronic kidney disease and dementia [2].

In pathological situations, such as hypertension, large amounts of reactive oxygen species (ROS) are released. If endogenous antioxidants cannot neutralise these, it leads to oxidative stress. Oxidative stress is closely involved in the development and progression of CVD [3].

Studies indicate elevated levels of malondialdehyde (MDA), 8-iso-prostaglandin, and oxidised LDL (oxLDL, a key marker of oxidative lipid damage) [4–6].

Individuals with a combination of CVD risk factors — such as abdominal obesity, dyslipidemia, high blood pressure, and glucose intolerance — are considered to have metabolic syndrome (MetS), which greatly increases their risk of developing CVD [7].

Preventing CVD is therefore extremely important. Lifestyle changes, such as dietary adjustments, physical activity, and smoking cessation, as well as medication, can help [8]. Due to the high prevalence of CVD, further research into antihypertensive and antioxidant therapies is needed.

Polyphenols in olive extract have antioxidant properties and may therefore be useful in combating oxidative stress [9]. Previous studies (including one by the NatuRAPT research group using a combination of olive extract and red yeast rice) have shown that olive extract can lower elevated blood pressure [10,11]. Additionally, olive polyphenols have a positive effect on cholesterol levels [12–14]. Several years ago, EFSA (European Food Safety Authority) approved a health claim (“protects LDL from oxidation”) for olive oil preparations related to a daily intake of 5 mg hydroxytyrosol [15,16]. Other studies have demonstrated an anti-hyperglycemic effect in individuals taking olive leaf extract for 12 weeks [17].

Olive polyphenols may therefore have a beneficial effect on various CVD risk factors.

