## 4. Trial Design

### 4.1 Description of Trial Design

This is a randomised, placebo-controlled, double-blind study. It includes 56 participants, equally divided into 2 groups (28 participants per group). One group will receive Tensiofytol®, and the other will receive a placebo.

Participation in this study will take a maximum of 10 weeks. The potential participant will be invited for a screening visit. If eligible, the participant will be randomised. The study product will then be delivered to the participant as soon as possible. Intake of the study product must start no later than 1 week after the screening visit. The participant must then take the study product or placebo daily. An interim blood pressure measurement will take place 4 weeks after starting intake. The final visit will be scheduled 8 to a maximum of 9 weeks after starting intake. After the final visit, the participant will be unblinded, marking the end of participation.

Participants will be stratified by sex and then randomised into 2 groups. This will occur 1 to 2 days after the screening visit, once all results are available.

This study is double-blind. The investigators do not know which group the participant is assigned to. The participant will be informed of the treatment they received during the final visit, after all data have been collected. The randomisation list and unblinding at the final visit will be handled by a separate study staff member responsible solely for these tasks.

This is a single-centre study. Participants will be enrolled by researchers from the NatuRAPT research group.

Statistical analysis will be performed after all data from all participants have been collected. No interim analysis is planned.

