### 5.3 Inclusion Criteria

To participate in this study, the potential participant must meet the following criterion:

1. An average systolic blood pressure  $\geq 130$  mmHg

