## 9. Statistical Considerations

### 9.1 Statistical Analysis

Demographic data and baseline values will be used to describe the study groups.

The difference in each parameter compared to baseline will be analyzed using ANCOVA by treatment group, adjusted for baseline values. An  $\alpha$ -level of 0.025 will be applied for the primary analysis. For secondary and exploratory analyses, an  $\alpha$ -level of 0.05 will be used.

The absolute change from baseline in blood pressure over time will be studied using Linear Mixed Models. Baseline value, treatment group, time point, and the interaction between treatment group and time point will be fixed variables. Participant ID will be a random variable.

As sensitivity or exploratory analyses, predictors such as sex, age, baseline values, or compliance may be added to the models to assess whether they have a significant effect.

Subgroup analyses may also be performed, and other continuous parameters can be studied using the same method.

No interim analysis is planned.

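### Section 9.2 describes its effect size as a fall after olive extract, yet the 25 per group follows only if that fall is the olive-minus-placebo difference; the 80% power leaves almost no room for a placebo change

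*Protocol*

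**What the plan says.** Protocol section 9.2 takes a systolic reduction of 10.4 ± 11.4 "mmHg after intake of olive extract [10,11"] from earlier studies as the basis for sizing. It sets the error rates ("level of 0.025 is used. The planned power is 80"%) and states: "It is calculated that at least 25 participants per group are needed to detect this effect". It then adds: "Considering an anticipated dropout rate of 10%, 28 participants per group (56 in total) will be recruited for this study". It gives no change under placebo, no difference from placebo, no test and no sidedness.

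The primary analysis in section 9.1 is a between-arm comparison: "The difference in each parameter compared to baseline will be analyzed using ANCOVA by treatment group, adjusted for baseline values". Section 4.1 confirms equal allocation: "It includes 56 participants, equally divided into 2 groups (28 participants per group").

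Two other places bear on the effect size. Section 5.3 admits people on one criterion, "An average systolic blood pressure" of at least 130 mmHg. Sections 1.3 and 8.1.1 show that this pressure is measured three times at the screening visit, the only scheduled visit before treatment, so the same measurements serve as baseline. Section 2.1 says of the earlier olive studies that they were "including one by the NatuRAPT research group using a combination of olive extract and red yeast rice" among others; the reference list shows that a study of that combination is one of the two sources cited for the 10.4 mmHg.

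**The concern.** A fall from baseline in people who took olive extract mixes any effect of the extract with whatever would have happened without it: regression to the mean, familiarity with the measurement, and any response to taking capsules. A randomised comparison with placebo removes those components, so the difference it can find is the treated-arm fall minus the placebo-arm fall. If a treated-arm fall is entered as the between-arm difference, the placebo arm is implicitly assumed not to change.

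Some fall in both arms is plausible here. Participants are selected for high systolic pressure at one visit, and that visit also supplies the baseline.

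What is at stake is the meaning of the 80%. It tells a reader how to take a non-significant primary result. If the real placebo-subtracted effect is smaller than 10.4 mmHg, the chance of missing it is larger than section 9.2 implies. Neither bias nor type I error is affected.

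**Working it through.** **Inputs.** From section 9.2: reduction 10.4 mmHg, SD 11.4 mmHg, alpha 0.025, power 80%, 25 per group, dropout 10%. From section 4.1: 1:1 allocation. Assumptions: the size of the placebo fall, and a residual SD of 9.9 after baseline adjustment (9.9/11.4 = 0.87, about 13% lower).

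**Formula.** Two-sample t-test with n per arm: noncentrality = Δ / (SD × √(2/n)), degrees of freedom 2n − 2. Power is the probability that the noncentral t exceeds the two-sided critical value in absolute terms.

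**Step 1: reproduce the plan's figure.** Standardised effect = 10.4/11.4 = 0.912. With n = 25, the standard error is 11.4 × √(2/25) = 3.224, the noncentrality is 10.4/3.224 = 3.225, and the critical value on 48 degrees of freedom at two-sided 0.025 is 2.314. Power is 81.6%. With n = 24 it is 79.7%, so 25 is the smallest sufficient number.

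Other readings of the same inputs give different numbers:

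| Calculation | n for 80% power |
|---|---|
| Two-sample t, two-sided 0.025 | 25 per group |
| Two-sample t, one-sided 0.025 or two-sided 0.05 | 20 per group |
| Paired (within-arm) t, two-sided 0.025 | 15 |

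Of these, only the between-arm test with the full 10.4 mmHg as the difference gives the stated 25. The dropout step is correct: 25/0.90 = 27.8, rounded up to 28.

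**Step 2: how much placebo change the 80% tolerates.** Solving for 80% power at SD 11.4 gives a difference of 10.2 mmHg with 25 per arm and 9.6 mmHg with 28. If 10.4 mmHg is a treated-arm fall, the tolerable placebo fall is 10.4 − 10.2 = 0.2 mmHg, or 10.4 − 9.6 = 0.8 mmHg if nobody drops out.

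**Step 3: power for assumed placebo falls, 25 per arm.** Net difference = 10.4 − placebo fall.

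| Placebo fall (assumed) | Net difference | Power, SD 11.4 | Power, SD 9.9 (assumed) |
|---|---|---|---|
| 0 | 10.4 | 82% | 92% |
| 1 | 9.4 | 72% | 85% |
| 2 | 8.4 | 62% | 75% |
| 3 | 7.4 | 50% | 63% |
| 5 | 5.4 | 27% | 36% |

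**Step 4: detectable difference with baseline adjustment.** At a residual SD of 9.9, 80% power corresponds to 8.9 mmHg with 25 per arm and 8.4 mmHg with 28. The degree of freedom spent on the covariate is ignored.

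**The case against.** The strongest objection is that the within-arm reading rests on wording alone. The protocol is a machine translation from Dutch, and the cited studies are not at hand. One of them is placebo-controlled by its title, so a placebo-subtracted value may have been available to the authors. A reader might infer that the protocol certainly used a before-after fall; the documents do not show whether 10.4 ± 11.4 is within-arm, net of placebo or pooled over two studies. This stands, and it limits the point to what section 9.2 says and fails to say.

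Second, a reader might infer that the 80% holds only if the placebo arm does not change at all. The planned ANCOVA does not support that. At a residual SD of 9.9, power is still 85% with a 1 mmHg placebo fall; if the SD were 20% lower than 11.4, it would be about 82% with a 2 mmHg fall. This also stands, but both gains are assumed, section 9.2 claims neither, and they do not offset falls of 3 to 5 mmHg.

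Third, the size of any placebo fall is unknown. Selection is on an average of three readings, not one, although all come from one visit. Regression to the mean depends on inputs the protocol does not give: with a source-population SD of 15, a mean of 125 to 140 and a visit-to-visit correlation of 0.7 to 0.8 (all assumed), the expected fall runs from 1.3 to 4.6 mmHg. Section 4.2 mentions a placebo effect only as a general reason for blinding and is no forecast. The red yeast rice component is disclosed, and nothing shows that it changed the 10.4 mmHg.

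Finally, the protocol itself states the effect, SD, alpha, power and number, so this is not a detail properly left to an analysis plan.

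**Conclusion.** The point holds in limited form. As worded, section 9.2 gives a treated-arm change, and its 25 per group follows only from using that figure as the between-arm difference. The stated 80% is therefore unsupported unless the figure is already net of placebo, the placebo arm barely changes, or baseline adjustment makes up the loss. On the protocol's own inputs the margin is 0.2 mmHg (0.8 with no dropout). For assumed placebo falls of 2 to 5 mmHg, power is 62% down to 27%, or 75% down to 36% at an assumed residual SD of 9.9.

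This should be fixed, but it does not threaten the trial's validity: only the power statement changes. Confidence is moderate because the source studies are not at hand. The two-sided test is inferred from the reproduction, not stated.

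**What to change.** Keep 56 participants. In section 9.2, state whether 10.4 ± 11.4 mmHg is a within-arm change or a difference net of placebo, and name the test and the two-sided alpha of 0.025. If the figure is net of placebo, saying so and giving the origin of the SD is enough.

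If it is within-arm, replace the 80% claim with text such as: *25 completers per arm give 80% power for a between-arm difference of 10.2 mmHg (unadjusted SD 11.4), or about 8.9 mmHg if baseline adjustment lowers the residual SD to 9.9; power for 7.4 mmHg is 50–63% and for 5.4 mmHg 27–36%.* Mark the 9.9 as an assumption, and add that a non-significant result does not exclude smaller effects.

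The cost is a rewritten paragraph and, in the within-arm case, a less favourable power statement. No participants, visits or analyses are added.

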## 10. General Considerations: Regulatory, Ethical, and Trial Oversight

### 10.1 Committees

The study is reviewed and reported to the Medical Ethics Committee of UZA/UAntwerp.

### 10.2 Informed Consent Process

Before the screening visit, the potential participant will receive the informed consent form (ICF) by mail. The participant must read this before the screening.

During the screening visit, the researcher will review the ICF with the participant, who may ask questions.

If the participant agrees, the ICF will be signed in duplicate. Both the researcher and the participant will receive a copy.

### 10.3 Data Protection

The identity and participation in this study will be treated with strict confidentiality. The participant will not be identified by name or in any other way in files, results, or publications related to the study. To guarantee privacy, data will be pseudonymized. All further processing will be carried out on these pseudonymized data. The link between the pseudonym and the individual will be retained only to allow certain information to be communicated back to the participant in their own interest.

The participant consents to the use of personal data collected for this study. This consent can be withdrawn at any time. If participation ends prematurely, the original consent allows the use of data collected during the period the participant was actively involved in the study. Only individuals directly involved in the study will have access to personal data. Data will not be shared with third parties. Researchers will retain the data for a period of 25 years.

The participant has the right to ask the researcher which data are collected and for what purpose. The participant may request corrections or deletion of certain data or ask that data no longer be used. All data will be handled in accordance with the “Directive on the protection of individuals regarding the processing of personal data” and applicable national legislation, including the European General Data Protection Regulation (GDPR – EU2016/679) and Belgian law implementing this regulation. Questions regarding data management can be addressed to the study physician or treating physician.

If the participant feels that their rights regarding personal data are not adequately respected, they may contact the Data Protection Officer, who will take appropriate measures. The participant also has the right to file a complaint with the Belgian Data Protection Authority. More information: <https://www.uza.be/privacy.html>.

## 10.4 Funding

This study was partly funded by the chair “Tilman – Olive Polyphenols and Cardiovascular Health.” Although Tilman funds the chair (budget includes salary for a part-time researcher, participant recruitment, study execution, report writing, blood sampling, participant travel costs, and publication costs), this is a non-commercial study with UAntwerp as the sponsor.

There was no contractual commitment regarding the study and the results.

Tilman had no methodological or any other input in the design, execution or reporting of this trial.

Tilman had no access to the detailed study protocol or raw study data.

Before starting the study, it was agreed that the results would be published, regardless of the outcome.

## 11. General Considerations: Risk Management and Quality Assurance

The quality of the study products is guaranteed by the manufacturer, Tilman.

The content of oleuropein and hydroxytyrosol in the study products will be verified by NatuRAPT.

